#### Sample size determination

According to several publications [36–40], the study aimed to determine the targeted difference of interest in CAP scores between the EPL arm and the placebo arm, which was set at 20 dB/m after 6 months. This difference was used in the sample size calculation, assuming a standard deviation of 45 dB/m.

A sample size of 162 patients (*n* = 81 per arm) is required for a 5% two-sided *T*-test to reach 80% power. The primary efficacy population is the mITT population. Assuming a drop-out rate of 15% (such as patients who discontinue the study drug after randomization or certain patients who never started the treatment), 190 patients (intention-to-treat [ITT] population) will be randomized at the beginning of the trial in order to reach the targeted number of 162 patients in the mITT population.

#### Analysis sets

The following analysis sets will be used in the statistical analyses.

• Screened set: All patients who sign the informed consent form.

• Randomization set (ITT): All patients from the screened set who are eligible for the trial based on the defined inclusion and exclusion criteria and are randomly assigned to the EPL arm or the placebo arm.

• mITT: All patients from the randomization set with evaluable CAP scores at baseline and at least one post-baseline CAP measurement and who actually received the randomized treatment (at least 80% of the study drug planned to be given within 6 months). All analyses using the mITT will be done according to the randomized treatment.

• Safety set: Patients who received at least one dose of the randomized treatment. All analyses using the safety set will be done according to the treatment received.

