### Discontinuation of study drug

In the event of permanent discontinuation of the study drug, all required assessments requested at the end-of-treatment visit (day 168 ± 7) and at the end-of-trial visit (day 252 ± 14) will be conducted. Patients who withdraw prematurely from the trial will undergo end-of-study visit assessments at an identified early trial discontinuation visit. All cases of permanent study drug discontinuation and patient’s withdrawal must be recorded by the investigator in the appropriate pages of the eCRF when confirmed.

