### Statistical analyses

#### Primary analysis

For the primary endpoint of change in the CAP score, as measured by transient elastography, from baseline to 6 months between the EPL arm and the placebo arm, the following statistical null and alternative hypothesis will be tested:H0: μA = μR.H1: μA ≠ μR.

where μX is change in the CAP score from baseline at month 6 for the treatment arms: EPL added to standard of care (X = A) and placebo added to standard of care (X = R). The planned statistical analysis involves utilizing a mixed-effects model with repeated measures (MMRM) to examine the hypothesis. The MMRM will incorporate several fixed categorical effects, including treatment arm, visit, country, and treatment-by-visit interaction term. Additionally, covariates such as the CAP score at baseline and the interaction between baseline CAP score and visit will be considered in the MMRM. Additional analysis will be done such as a linear mixed model (LMM) with the same fixed categorical effects and covariates as the primary MMRM, and will be used for sensitivity analysis based on multiple imputed datasets (e.g., 100 datasets). The final statistical inference, including parameter estimates and standard error estimates, will follow Rubin’s formula [35]. The statistical test will be two-sided and conducted at a significance level of 5%, resulting in 95% confidence intervals (CIs) (CIs; two-sided). A *p*-value less than 0.05 will be considered statistically significant. The analysis will be based on the modified intention-to-treat (mITT) population.

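### The primary mITT set keeps only patients who took at least 80% of the planned 6-month drug, so the primary comparison is no longer protected by randomisation

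*Protocol article*

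**What the plan says.** Primary analysis section of the protocol article, on the MMRM: "The analysis will be based on the modified intention-to-treat (mITT) population". Sample size determination repeats it: "The primary efficacy population is the mITT population".

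Analysis sets defines the mITT by two conditions that are met only after randomisation:

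- CAP data: "All patients from the randomization set with evaluable CAP scores at baseline and at least one post-baseline CAP measurement".
- Drug intake: patients "who actually received the randomized treatment (at least 80% of the study drug planned to be given within 6 months".

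It adds: "All analyses using the mITT will be done according to the randomized treatment".

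Three other sections bear on this:

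- Sample size determination allows for 15% loss between the 190 randomised and the 162 in the mITT, and counts patients who stop the drug or never start it within that loss.
- Discontinuation of study drug keeps measuring patients who stop: "In the event of permanent discontinuation of the study drug, all required assessments requested at the end-of-treatment visit" and at the end-of-trial visit are still to be done.
- Estimands and intercurrent events names death and discontinuation for a treatment-emergent adverse event as possible intercurrent events, with a hypothetical strategy for the primary endpoint.

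A full randomised (ITT) set is defined, but the article assigns it no efficacy analysis.

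**The concern.** Randomisation makes the arms comparable at the start. If patients are then kept or dropped according to what they did over the next 6 months, the retained groups are comparable only if the dropping works the same way in both arms. Taking 80% of the drug can depend on how well it is tolerated and on whether the patient sees benefit. The Introduction lists gastrointestinal and skin reactions as identified risks of EPL, so the reasons for falling below 80% could differ by arm.

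The rule also sits badly with the rest of the plan. Most adverse-event discontinuers would leave the set before the hypothetical strategy could be applied to them, and that strategy calls for modelling an outcome, not for removing the patient. Patients who fall short for any other reason are not covered by a listed intercurrent event, yet they are removed too, although the trial still measures those who stop the drug.

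At stake are the validity of the primary p-value and confidence interval, and a population label that suggests an analysis close to intention-to-treat.

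**Working it through.** **1. The plan's own sample size.** Inputs from Sample size determination: a difference "which was set at 20 dB/m after 6 months", "assuming a standard deviation of 45 dB/m", two-sided 5% t-test, 80% power.

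- Noncentral-t power with 81 per arm is 0.803, and with 80 per arm 0.798. So 81 per arm (162) reproduces.
- 162 / 0.85 = 190.6, and 190 × 0.85 = 161.5. So 190 reproduces within rounding.
- The plan therefore expects 190 − 162 = 28 randomised patients to be outside the primary set. The arithmetic is sound; the problem is the population to which it is applied.

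**2. What the threshold means.** Six capsules a day for 168 days is 1008 capsules.

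- 0.80 × 168 = 134.4 days; 0.80 × 1008 = 806 capsules.
- A fully adherent patient who stops at Visit 2 (day 84) has taken 84/168 = 50% and is excluded, even with CAP measured at Visits 2 and 3.

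**3. How large a bias could be.** Let f be the fraction excluded in an arm, and d the amount (dB/m) by which the excluded patients' mean CAP change is worse than that of the retained patients. The retained mean is then the full-arm mean minus f × d, so

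bias in (EPL − placebo) = −(f_EPL × d_EPL − f_placebo × d_placebo),

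where a negative value favours EPL. With no true effect, type I error = P(|Z + bias/SE| > 1.96). **The article gives neither f by arm nor d; every value in the table is an assumption.** There are 95 randomised per arm and the SD is 45.

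| Excluded, EPL / placebo | d (both arms) | Bias (dB/m) | Type I error |
|---|---|---|---|
| 15% / 15% | any equal value | 0 | 5.0% |
| 20% / 10% | 20 | 2 towards EPL | 5.9% |
| 20% / 10% | 40 | 4 towards EPL | 8.7% |
| 10% / 20% | 20 | 2 against EPL | 5.9% |
| 10% / 20% | 40 | 4 against EPL | 8.7% |

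For the 20%/10% rows, 76 and 85.5 patients remain, so SE = 45 × √(1/76 + 1/85.5) = 7.09. For d = 20, bias/SE = 2/7.09 = 0.28; for d = 40, it is 0.56. A shift of 2 to 4 dB/m is 10% to 20% of the 20 dB/m target.

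**4. Power if the threshold is removed.** Two-sample t-test, SD 45. Dilution is illustrated by assuming that 15% of the EPL arm gains nothing: 20 × 0.85 = 17 dB/m.

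| Patients contributing CAP | Power at 20 dB/m | Power at 17 dB/m |
|---|---|---|
| 190 | 86% | 74% |
| 180 | 84% | 71% |

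Under that dilution, 80% power would need 222 patients (111 per arm).

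**The case against.** Several points on the other side are fair.

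- **Blinding.** The trial is double-blind with matching placebo. If EPL affects neither tolerability, adherence nor CAP, exclusion is the same in expectation in both arms and the test keeps its level. This stands: a reader might infer that the 5% level is actually breached, and the article does not show that. It shows only that nothing guarantees the level.
- **Direction.** A reader might infer that the rule favours EPL. The article gives no adverse-event rates by arm and says that the frequency of the known risks is mostly unknown, so bias could go either way or be nil.
- **Lifestyle.** It is tempting to argue that patients who take their capsules also follow diet and exercise advice. That is plausible, but nothing in the article supports it, and the point does not need it.
- **Discarded data.** For patients who stop because of an adverse event, the hypothetical strategy itself implies setting off-drug CAP aside. The complaint about unused measurements therefore holds only for other non-adherers.
- **Label.** The set is not a full per-protocol set: it screens on intake and CAP availability, not on protocol deviations generally.

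Three defences do not hold. Analysis by randomised arm fixes the arm label, not who is selected. The Adherence section counts capsules up to discontinuation, but that describes the amount taken; the mITT condition is set against the drug planned for 6 months, and the sample size text counts discontinuers as lost. Finally, an SAP not shown here may add a supportive ITT analysis, but the primary set is fixed in the article.

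**Conclusion.** The point holds as a defect in the choice of primary population. The primary set is selected on behaviour after randomisation, nothing elsewhere in the article undoes the rule, and the sample size is built on it. The comparison loses the protection of randomisation and the 5% error rate is no longer guaranteed.

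How much this matters in practice is unknown. The shift of 2 to 4 dB/m and the error rate of 5.9% to 8.7% are illustrations that rest on assumed exclusion rates and deficits, and they apply in either direction. The firm figures are the threshold (about 134 of 168 days) and the planned loss of about 28 of 190 patients. Because the primary test is affected and a change of wording repairs it, the change should be made before unblinding.

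**What to change.** Before unblinding, in the protocol or SAP:

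1. Make the primary MMRM population all randomised patients, analysed as randomised, with no adherence threshold. Patients without any post-baseline CAP are handled by the model or by the imputation already planned.
2. Keep the 80% set as a supportive analysis and name it as a per-protocol-type set.
3. Reconcile this with the estimand section. State whether CAP measured after discontinuation for an adverse event is set aside and modelled (hypothetical strategy) or used (treatment policy). Removing the threshold does not settle this, and using all such CAP without saying so would change the stated estimand. CAP after other non-adherence is used.
4. Restate the power for the new population.

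No new data are needed. The cost is possible dilution: undiluted power rises above the planned 80%, but it falls to about 74% if 15% of the EPL arm gains nothing, and to about 71% if only 180 patients contribute CAP. The article reports that recruitment was complete by August 2023, so the sample size cannot easily be raised to offset this.

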#### Subgroup analyses

Subgroup analyses will be performed depending on the final sample size and data availability for the primary and secondary endpoints. At least 1 subgroup analysis based on CAP score at baseline (< 288 dB/m, ≥ 288 dB/m) will be performed.

#### Adverse events

The incidence of adverse events will be presented by treatment arm in the order of system organ class, with information on high-level group term (HLGT), high-level term (HLT), and preferred term (PT) sorted in alphabetical order. For each treatment arm, the number (*n*) and percentage (%) of patients who experience each adverse event would be recorded. If the same adverse event occurs multiple times in the same patient during a treatment phase, it will only be counted once. The denominator used for calculating the percentages will be the safety population within each treatment arm.

#### Missing data

To impute missing values for post-baseline visits, the approach of utilizing a pattern-mixture model with control-based pattern imputation [41–43] will be adopted.

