### Estimands and intercurrent events

For efficacy analysis, estimand framework will be used in this trial. The possible ICE (intercurrent events) type may be death due to any cause or discontinuation of study drug due to treatment-emergent adverse event. For the primary endpoint of change in steatosis, as measured by transient elastography (CAP score), from baseline to 6 months, the ICE strategy is hypothetical.

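### The 80%-exposure mITT removes most drug discontinuers before the hypothetical strategy or the control-based imputation can act, so the planned sensitivity analysis barely tests dependence on drop-out

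*Protocol article*

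**What the plan says.** All references are to the protocol article.

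- **Estimands and intercurrent events.** The possible events are "death due to any cause or discontinuation of study drug due to treatment-emergent adverse event". For change in CAP at 6 months, "the ICE strategy is hypothetical".
- **Primary analysis.** "The planned statistical analysis involves utilizing a mixed-effects model with repeated measures (MMRM) to examine the hypothesis". A linear mixed model with the same terms "will be used for sensitivity analysis based on multiple imputed datasets (e.g., 100 datasets"). On population: "The analysis will be based on the modified intention-to-treat (mITT) population". No other set is named for the imputed analysis.
- **Analysis sets.** The mITT needs a baseline CAP, one or more later CAP values, and patients "who actually received the randomized treatment (at least 80% of the study drug planned to be given within 6 months"). A month 6 CAP is not required.
- **Missing data.** One sentence: "To impute missing values for post-baseline visits, the approach of utilizing a pattern-mixture model with control-based pattern imputation" will be adopted. It does not say which analysis it serves.
- **Sample size determination.** 162 patients in the mITT are reached from 190 randomised by allowing 15% drop-out, and patients who stop the drug are given as an example of drop-out.
- **Discontinuation of study drug.** Patients who stop permanently still have the end-of-treatment and end-of-trial assessments.

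**The concern.** The hypothetical strategy and the imputation both exist to deal with patients whose course was interrupted. The mITT selects on drug intake after randomisation and takes most of those patients out first. Three things follow.

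1. The primary comparison is between two groups of adherers, not between the groups as randomised. The stated estimand is not what is estimated for patients who stop early.
2. The sensitivity analysis has few discontinuers to act on. Close agreement with the MMRM would say little about whether the result depends on drop-out, although it could be read as robustness.
3. For the patients it does reach, control-based imputation gives EPL patients placebo-like values. That is not the CAP they would have had if the intercurrent event had not occurred, so the analysis answers a different question from the stated estimand.

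**Working it through.** **Plan's own figures.** With a difference of 20 dB/m, SD 45 and a two-sided 5% t-test, power is 79.8% at 80 per arm and 80.3% at 81 per arm, so 162 is reproduced. For drop-out, 162/0.85 = 190.6 and 190 × 0.85 = 161.5, so 190 agrees apart from rounding. The plan therefore places 190 − 162 = 28 patients (28/190 = 14.7%) outside the mITT.

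**Where the 80% rule cuts.** Six capsules a day for 168 days is 1,008 capsules, and 80% is 806.4. At full dosing that is 806.4/6 = 134.4 days (128.8 to 140.0 if Visit 3 falls on day 161 to 175). Only stops in the last 168 − 134.4 = 33.6 days can stay in the mITT, and missed doses earlier on narrow that window.

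**How far the imputation can move the result.** Assume imputed EPL patients take the placebo mean at month 6 (jump-to-reference; the article does not name the variant), with equal stopping by arm. If a share f of the EPL arm is imputed:

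effect = 20 × (1 − f)

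With a proportion d stopping and a share s of stops late enough to stay, all of these lacking a month 6 CAP:

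f = 190·d·s / (190 − 190·d + 190·d·s)

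The documents give neither s nor the number of missing month 6 scans, so these are assumptions. Stops spread evenly over 168 days give s = 33.6/168 = 20%. Stops spread evenly over days 84 to 168 give s = 33.6/84 = 40%.

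| d | s | imputable | mITT | f | effect, mITT (dB/m) | effect, all 190: 20 × (1 − d) |
|---|---|---|---|---|---|---|
| 15% | 0 (plan's accounting) | 0 | 161.5 | 0 | 20.0 | 17.0 |
| 15% | 20% | 5.7 | 167.2 | 3.4% | 19.3 | 17.0 |
| 15% | 40% | 11.4 | 172.9 | 6.6% | 18.7 | 17.0 |
| 10% | 20% | 3.8 | 174.8 | 2.2% | 19.6 | 18.0 |
| 25% | 60% | 28.5 | 171.0 | 16.7% | 16.7 | 15.0 |

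Over d = 10-25% and s = 0-60%, the mITT result lies between 20.0 and 16.7 dB/m.

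**Missed or unusable Visit 3 scans in adherent patients.** At an assumed 2-10% of 162, 3.2 to 16.2 patients are imputed and the effect is 19.6 to 18.0 dB/m.

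**What the fuller test would mean.** At 95 per arm and SD 45, t-test power is 86.2% for 20 dB/m and 73.6% for 17.0 dB/m. The 17.0 assumes that all of the 15% are imputed. The shrinkage from imputation is less if CAP measured after discontinuation is used.

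**The case against.** **The passages do not conflict.** A reader might infer that control-based imputation contradicts the hypothetical strategy outright, or that the same missing values are given two rules. The documents do not support this. The Primary analysis section tests the hypothesis with an MMRM, which assumes missing at random and fits a hypothetical strategy, and it places multiply imputed data in a sensitivity analysis. The natural reading is that the Missing data section supplies the model for that sensitivity analysis. There would be a contradiction only if imputation governed the primary MMRM, and nothing says so. This stands, and leaves only a request for one clarifying sentence.

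**The mismatch is partial.** The listed events are death and discontinuation due to a treatment-emergent adverse event. Other withdrawals and missed scans are ordinary missing data, and imputing them conservatively does not conflict with the strategy. Control-based imputation is also a recognised conservative analysis. Both points stand; the objection is to its use as the only sensitivity analysis of a hypothetical estimand.

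**Some patients remain to be imputed.** A reader might infer that the analysis has nothing to work on, or that its effect has a fixed small ceiling. Neither is shown. Late stoppers and patients without a usable Visit 3 scan stay in the mITT, and if many stop late the shift is not small (bottom row of the table).

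**The counting window could differ.** The Adherence section counts capsules up to discontinuation. If the 80% rule used expected capsules over that shorter window, some early stoppers with a Visit 2 scan would stay in. The mITT wording refers to drug planned over 6 months, which points the other way. The two sections should be reconciled.

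**The root cause is the mITT definition.** This is correct, and the fix starts there.

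**Conclusion.** The point holds as a weakness of design, not as a contradiction. The exposure rule, applied after randomisation, removes patients who stop before about day 134, and the plan's own accounting puts discontinuers among the roughly 28 of 190 outside the mITT. With 15% stopping and 20-40% of stops late, the imputation moves a 20 dB/m effect by about 0.7 to 1.3 dB/m, against 3.0 dB/m if 15% of all randomised patients were imputed. On the plan's own accounting, drop-out moves it by nothing.

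These sizes rest on assumed stopping times, equal stopping by arm, placebo-mean imputation and no month 6 CAP in late stoppers. The wider range is 20.0 to 16.7 dB/m, so the plan is a weak test rather than no test. Separately, and whatever the population, control-based imputation does not target the hypothetical estimand for the two listed events.

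**What to change.** 1. Run the primary MMRM and all missing-data analyses in all randomised patients with a baseline CAP, analysed as randomised. For the hypothetical estimand, set CAP after a listed intercurrent event to missing. Keep the 80%-exposure set as a supplementary analysis.
2. Add delta-adjusted (tipping-point) multiple imputation as the sensitivity analysis of the hypothetical estimand. Keep control-based imputation as a supplementary conservative analysis, and state what it estimates.
3. State under Missing data that imputation serves the linear mixed model analyses and not the primary MMRM. Reconcile the capsule-counting window under Adherence with the 80% rule, which still defines the supplementary set.

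Cost: wording changes and one extra imputation run, made before unblinding. No new data are needed, because end-of-treatment assessments after discontinuation are already scheduled. The downside is that the estimated effect may be smaller than among adherers.

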#### Demographics and baseline characteristics

Descriptive statistics will be used to aggregate data in tables, listings, and figures, as appropriate. Continuous variables will be described with summary statistics, such as *n*, mean, standard deviation (SD), median, the first and third quartiles (Q1 and Q3), and minimum and maximum values.

For each categorical variable, the frequency and percentage in each category will be reported. Percentages will be calculated using the specified denominator in the table based on a given analysis set. Missing data may be included as a separate category in some scenarios, depending on the nature of the variable. Confidence intervals of 95% will be calculated when relevant.

For binary analysis mainly the exploratory endpoints would be considered and for each categorical variable of an exploratory endpoint, a logistic regression or chi-square test will be considered. No formal testing will be done on the demographics.

The statistical analysis will be performed using SAS statistical software, Version 9.4 or higher or SAS Enterprise Guide 7.1 or higher.

### Dissemination plans

The results of this trial may be published or presented at scientific meetings.

## Discussion

The treatment of MASLD generally involves making lifestyle changes, such as modifying diet and engaging in regular exercise to achieve weight loss [44, 45]. Although extensive research and numerous clinical studies have been conducted, there is currently no universally accepted “gold standard” for the treatment of MASLD [1, 23]. More recently, the U.S. Food and Drug Administration approved resmetirom for the treatment of adults with noncirrhotic non-alcoholic steatohepatitis with moderate to advanced liver fibrosis, to be used along with diet and exercise [46]. So far, long-term effects about safety and efficacy of resmetirom treatment are unknown. Furthermore, resmetirom treatment in patients with MASLD did not improve estimates of insulin resistance [47], which may be important to decrease the elevated cardiometabolic risk that is often observed in patients with MASLD [48]. In addition, resmetirom was specifically approved only for patients having steatohepatitis.

EPL have shown to improve liver steatosis in patients with MASLD associated with obesity, diabetes mellitus, and dyslipidemia in several randomized controlled clinical trials, including placebo-controlled studies [28–31, 49]. In addition, EPL also evidently improved liver function tests and treatment adherence and satisfaction as shown in several observational studies. Real-world observational research showed that the administration of EPL lowered levels of aspartate aminotransaminase (AST), alanine aminotransaminase (ALT), and GGT in MASLD patients, regardless of the presence or number of associated comorbidities [50]. In a pooled analysis of 3 observational studies in patients with MASLD, significant improvements in transaminases and lipid levels and steatosis were observed following 24 weeks of EPL treatment, which translated to better treatment adherence and satisfaction [51].

However, the available evidence regarding the efficacy of EPL as an adjunctive MASLD treatment would need an objective assessment of fatty liver changes as well as an assessment of subjective improvement as measured by symptoms score and for the first time by validated QoL score and satisfaction and adherence to treatment. Therefore, to explore further aspects of EPL in the treatment of MASLD associated with T2DM and/or hyperlipidemia and/or obesity, this randomized controlled clinical trial has been designed to gain scientific data on the physical, functional, and QoL-related outcomes for patients.

Previous clinical studies utilized invasive techniques such as liver biopsy and noninvasive techniques such as transabdominal ultrasonography and FibroScan for the detection and measurement of steatosis and fibrosis in MASLD patients treated with EPL. However, these noninvasive techniques are effective only if the steatosis is greater than 30% [52]. In this study, we utilize a noninvasive approach by transient elastography (FibroScan) to evaluate the severity of MASLD by measuring both steatosis (CAP evaluation) and fibrosis (LSM evaluation) [19]. The CAP has shown high sensitivity in detecting low-grade steatosis, defined as fat deposition of 10% or higher. Therefore, the CAP provides a standardized, noninvasive measure for assessing the degree of hepatic steatosis [17, 53]. This will help in the assessment and continuous monitoring of the primary outcome in changes from baseline to 6 months to observe whether there is regression of the disease conditions (such as fibrosis, MASH, and steatosis).

For the first time, this trial will also evaluate changes of QoL parameters, as measured by the CLDQ-MASLD/MASH, a validated questionnaire specific for MASLD/MASH.

In this trial, to minimize the placebo effect we have created an optimized timeline of visits by the investigator to ensure appropriate trial intervention. We will also try to adopt 2016 EASL guidelines [32] for standard-of-care parameters such as diet and physical exercise across all trial sites. Patients participating in the clinical trial would be monitored for safety and medical care throughout the trial period.

The study has a limitation of excluding patients who consumed alcohol, > 20 g/day in women and > 30 g/day in men, i.e., patients with MetALD. Future studies might explore the potential of EPL in MetALD patients.

In summary, our study aims to utilize a rigorous design to comprehensively explore the efficacy of EPL in patients with MASLD on hepatic steatosis and patient-reported indices such as QoL and its safety in MASLD associated with T2DM and/or hyperlipidemia and/or obesity by assessing various outcome measures.

